**Protocol Section**

1. **Lay Summary (Max. 200 words)**

*Please provide a succinct overview of your proposed research in plain English i.e. non-technical language. This should cover the background, purpose of the study and the potential importance of the findings. References and abbreviations should be avoided. If you have ticked the "other" box in response to question 4 on the application form, up to an additional 100 words should be used to describe the benefit to public health expected from the study.*

Increasing numbers of people have more than one long term illness, such as diabetes or depression. While healthcare delivery and research has traditionally focused on treatment of individual diseases, the presence of two or more chronic diseases, known as multimorbidity, has become an increasingly common medical issue. Individuals with multimorbidity tend to have more complicated healthcare needs, often leading to increased doctors visits and hospitalisations.

The primary aim of this study is to use routinely collected medical record data to describe the prevalence of multimorbidity in English adults. We will examine the percentage of people in a sample of English patients that have multimorbidity, and the association of individual characteristics including age, sex, and ethnicity with multimorbidity. Additionally, we will assess the association of multimorbidity with usage of health services based on a patient’s number of GP visits, number of prescriptions, and how often they are admitted to hospital.

This work has the potential to benefit patients and health service providers. Through understanding how sociodemographic characteristics impact multimorbidity, we may be able to more appropriately target interventions for multimorbid patients. Additionally, it will allow for better planning and distribution of resources to better care for patients suffering from multimorbidity.

1. **Technical Summary (Max. 200 words)**

*Please provide a succinct overview of the objectives, methods and data analysis for the proposed research. Avoid the use of references in this section*.

Multimorbidity is becoming increasingly prevalent in England, and the effective management of multimorbid patients should be a priority of primary care medicine. In order to effectively plan health services to treat multimorbid patients, we must understand the epidemiology of this condition, and the current relationship between multimorbidity and health service usage.

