1. To use a representative, random sample of a large cohort of adult patients (≥18 years old) registered to an English general practice to describe the epidemiology of multimorbidity by sex, age, ethnicity, socioeconomic status, smoking status, and region.
2. To describe the frequency of pairs of two comorbid conditions in order to identify which morbidities most commonly present together.
3. To describe the relationship between the presence of mental health comorbidities and the number of physical morbidities an individual has.
4. To describe the utilisation of health services by individuals with multimorbidity based on the number of yearly GP consultations, the number of annual prescriptions dispensed, and the number of hospital admissions.
5. To determine patterns of multimorbidity disease combinations associated with health service utilisation outcomes, in order to identify clusters of patients that are in some respect “similar.”
6. **Background**

*Please provide a succinct review of the relevant background literature with references so as to explain the purpose of the study. Please ensure that you refer to any previous research in CPRD that is related, providing published references and, when known, the ISAC Protocol Number.*

The current paradigm for medical research tends to focus single diseases. This prioritisation of the study of individual diseases and treatments often excludes patients suffering from multiple chronic illnesses^2^. However, one of the central components of a strong primary care system is caring for the entire patient rather than focusing on a particular body system or disease^3^. As the UK population ages and more patients develop multiple chronic conditions, management of multimorbidity will become an increasingly important aspect of primary care medicine and research.

The current literature suggests that a substantial part of the population has multimorbidity, and while there are some discrepancies in the estimates of prevalence, these differences may be largely attributed to differences in defining morbidities. In Scotland, Barnett, *et al.*’s 2012 study found that 23.3% of all registered patients age 16 and older had two or more morbidities^4^, while Salisbury, *et al.* (2011) found the prevalence of multimorbidity to be 16% in UK adults^5^. This burden of multimorbidity places large demands on GPs, because it has been reported that multimorbid patients account for 78% of GP consultations^6^.

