To meet our first aim of describing the epidemiology of multimorbidity, we will estimate the prevalence of multimorbidity and explore how this may differ according to patient-level characteristics. We will use a chi-square test to examine differences in presence of multimorbidity (0-1 morbidities versus 2+ morbidities) in relation to sociodemographic characteristics outlined above. We will use a t-test to assess differences in the mean number of morbidities by sex, and one-way ANOVA to test differences in the mean number of morbidities by age (which will be categorised in 10-year age intervals), ethnicity, socioeconomic status (IMD deciles), smoking status, and region.

To meet our second aim of investigating the frequency of pairs of two comorbid conditions, we will describe the prevalence of frequently occurring disease pairs, which we consider to be any pair of comorbidities with a prevalence >5%. These pairs will be identified by calculating the prevalence for all 630 ( $\frac{36*35}{2}$) potential disease couplets, and then reporting the comorbidity pairs with >5% prevalence. As this is a descriptive study, we are primarily interested in identifying the most commonly occurring disease couplets, and describing their prevalence. Clinical appraisal of the most prevalent couplets will be conducted to establish whether these pairs are common because of a causal link, or common because each has relatively high prevalence. These differences will be addressed in our discussion. A chi-squared test will be used to evaluate the association of these co-occurring morbidity pairs (e.g. having the comorbidity pair of interest versus having a different combination of comorbidities) in relation to sociodemographic characteristics. A one-way ANOVA test will be used to assess differences in the mean number of morbidities an individual has given that they have a specific pairing of commonly occurring comorbid diseases.

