To meet our third aim of examining mental morbidities and the linkage of physical and mental comorbidities, we will report the percentage of individuals with both a physical and mental comorbidity. We will use a logistic regression, controlling for sociodemographic characteristics, to quantify the association between mental and physical morbidities, with the binary outcome being the presence of a mental health comorbidity. We will report odds ratios and covariate adjusted odds ratios of having any mental health disorder based on the number of physical morbidities an individual has. We will also report the odds ratios by sociodemographic characteristics. Additionally, we will use a chi-squared test to assess differences between the prevalence of any multimorbidity and the prevalence of having a physical-mental health comorbidity between our sociodemographic covariates described in Section K.

To meet our fourth aim of describing health service utilisation, we will use the total number of consultations as the denominator to evaluate the proportion of consultations devoted to patients with different levels of multimorbidity. We will also use the mean and standard deviation of the number of consultations and prescriptions to describe consultation and prescribing rates in relation to the number of morbidities. We will calculate the total number of consultations, prescriptions, and hospitalisations a patient has during our four-year study period, and will explore the patterns of the data to determine the most appropriate form of regression to look at the separate relationships between the number of morbidities and the number of consultations, prescriptions, and hospitalisations. In this analysis, we will adjust for patients who died during the four-year follow-up as well as for patients who have been censored due as a result of transferring out of the practice. We will use a Cox proportional hazards model to describe the differences in mortality rate between exposed multimorbidity patients and non-multimorbid patients. All regression analyses will consist of a crude analysis in addition to an adjusted one incorporating the covariates described in Section K.

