To meet our fifth aim of determining patterns of multimorbidity associated with health service utilisation outcomes, we will use a latent class analysis (Hagenaars *et al.* 2002) to classify patients according to their distribution of multimorbidities^25^. Within each class of patients, we will assume a distinct multivariable model of health service utilisation outcome. This approach will assist in the identification of class specific factors associated with health service usage. Ideally, we want to fit models including random effects to allow for variation between practices. Depending on the number of classes obtained, this could potentially be quite a big model with a large number of parameters. If appropriate, we will investigate sub-sampling methods for this data set, choosing a suitable representative sample on which to run the chosen models^26^.

1. **Plan for addressing confounding**

*Purely descriptive studies are exempt from this requirement. All other studies should here provide some discussion of what they are doing in the design and/or analysis to control for confounding.*

We will adjust for confounding using multivariable regressions with random-effects models to account for age, sex, socioeconomic deprivation, ethnicity, smoking status, and region, as well as for clustering by GP practice.

1. **Plan for addressing missing data**

*The potential for missing data should be identified and how it will be addressed discussed here.*

We will only use patients with complete age, gender, and IMD data. To reduce the proportion of patients with missing IMD data, we will only use linked practices. Patterns of missingness in the data set will be described and explored at an early stage, and we will consider using multiple imputation techniques where appropriate^27,28^. Missing data for smoking status will be imputed using the last observation carried forward method.

1. **Limitations of the study design, data sources and analytical methods**

*The general limitations of the databases and observational research are well-known. Specific consideration of the potential impact of such limitations should be provided in the context of the proposed study.*

The key limitations to this protocol are as follows:

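### The Aim 1 comparisons by ethnicity, deprivation, smoking and region are specified as unadjusted single-factor tests, and the protocol's age-adjusted regression is not linked to any model with multimorbidity as outcome

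*Protocol*

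**What the plan says.** Aim 1 (Objectives, Specific Aims and Rationale) is to "describe the epidemiology of multimorbidity by sex, age, ethnicity, socioeconomic status, smoking status, and region".

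The Data/Statistical Analysis section fixes the method:

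- Two or more morbidities against none or one: "We will use a chi-square test to examine differences in presence of multimorbidity (0-1 morbidities versus 2+ morbidities) in relation to sociodemographic characteristics".
- Number of morbidities by sex: "We will use a t-test to assess differences in the mean number of morbidities by sex".
- Number of morbidities by the other characteristics: "one-way ANOVA to test differences in the mean number of morbidities by age (which will be categorised in 10-year age intervals), ethnicity", then IMD decile, smoking status and region in the same way.

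For Aim 2, a chi-squared test compares common disease pairs across the same characteristics. No standardisation, stratification or regression is named for any of these comparisons.

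Adjustment appears in three other places. Aim 3 has a covariate-adjusted logistic regression, with a mental health comorbidity as the outcome. The Aim 4 paragraph, on utilisation and mortality, ends with "All regression analyses will consist of a crude analysis in addition to an adjusted one" using the Section K covariates. The Plan for addressing confounding says: "We will adjust for confounding using multivariable regressions with random-effects models to account for age, sex, socioeconomic deprivation, ethnicity, smoking status, and region", and also for clustering by practice. It does not say which aims it covers.

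On interpretation, the section on exposures and outcomes says that the primary objective is descriptive and has no specific exposure. The linkage section nevertheless calls deprivation and ethnicity predictors of multimorbidity, and the Lay Summary says: "Through understanding how sociodemographic characteristics impact multimorbidity, we may be able to more appropriately target interventions for multimorbid patients".

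**The concern.** The number of chronic conditions rises with age, and groups defined by ethnicity, deprivation, smoking or region may differ in age. A one-factor test then mixes two things: how common multimorbidity is at a given age, and how old the group is. For planning services the mixture is a useful quantity. For saying that a characteristic predicts or affects multimorbidity, it is not.

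The comparisons belong to the primary objective. Ethnicity, smoking status and region are also among the additions that the Background claims over the Scottish study that this work extends. If the analysis follows the Data/Statistical Analysis section literally, a younger group with more multimorbidity at every age could appear to have less. Ordinary chi-square and ANOVA also ignore the clustering by practice that the confounding section undertakes to handle.

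**Working it through.** **1. Which adjustment reaches which outcome**

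| Analysis | Outcome | Method stated | Age taken into account? |
| --- | --- | --- | --- |
| Aim 1 | 2+ morbidities; number of morbidities | chi-square, t-test, one-way ANOVA | no |
| Aim 2, pairs by covariate | having a given pair | chi-square | no |
| Aim 3 regression | mental health comorbidity | logistic, crude and adjusted | yes |
| Aim 4 | consultations, prescriptions, admissions, mortality | regression, Cox; crude and adjusted | yes |
| Confounding section | none named | random-effects multivariable regression | yes, but tied to no aim |

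The crude-plus-adjusted rule applies to regressions, and Aim 1 contains none. The confounding section is not limited by aim, so it could be meant to cover Aim 1, but there is no stated model for it to act on. The amendments change the clustering work and leave the Aim 1 tests as they are.

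**2. The plan's own figure**

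The Sample Size section uses n = Z²P(1−P)/d² with P = 23.2% and d = 0.13%:

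1.96² × 0.232 × 0.768 / 0.0013² = 405,018 (stated: 405,000).

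405,000 / 0.952 = 425,421, rounded up (stated: 425,400).

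Both reproduce. The calculation concerns overall prevalence and is untouched by this point.

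**3. What age mix alone can do (assumed inputs)**

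The documents give no age-specific prevalence and no age mix by group, so every input in this step is an assumption. Crude prevalence is the sum over age bands of age share × prevalence in the band. Take 8/28/62% at 18-44/45-64/65+, identical in both groups:

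- Group A (44/33/23%): 0.44×0.08 + 0.33×0.28 + 0.23×0.62 = 0.0352 + 0.0924 + 0.1426 = 27.0%.
- Group B (65/26/9%): 0.65×0.08 + 0.26×0.28 + 0.09×0.62 = 0.0520 + 0.0728 + 0.0558 = 18.1%.
- Crude odds ratio, B against A: (0.1806/0.8194)/(0.2702/0.7298) = 0.60. The within-age odds ratio is 1.00.
- With 365,000 patients in A and 40,000 in B, pooled prevalence is 0.2614 and chi-square = 0.0896² / [0.2614×0.7386×(1/365,000 + 1/40,000)] ≈ 1,500.

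Now give group B a true odds ratio of 1.5 in every band. Its band prevalences become 11.5/36.8/71.0%, and its crude prevalence is 0.65×0.115 + 0.26×0.368 + 0.09×0.710 = 23.5%. Against 27.0% the crude odds ratio is about 0.83, so the direction is reversed.

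**4. Range over other assumptions**

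Four bands (18-44/45-64/65-84/85+), with prevalences from 12/25/45/55% to 5/30/70/85%. The age mixes run from 45/34/18/3% against 50/32/15.5/2.5% to 40/35/21/4% against 70/23/6/1%.

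- No within-age difference: the crude gap runs from 1.3 points (23.65% against 22.35%, odds ratio 0.93) to 15.2 points (30.6% against 15.45%, odds ratio 0.41).
- Within-age odds ratio of 1.30 in the younger group: the crude odds ratio runs from 1.18 down to 0.50.

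**5. Sensitivity of the tests at this sample size**

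Two equal halves of 405,000 differ significantly at the 5% level from 1.96 × √(0.232×0.768×4/405,000) = 0.26 points. Two IMD deciles of about 40,500 (405,000/10) have 80% power for a difference of about 0.84 points from 23.2%. Every age-mix gap in steps 3 and 4 exceeds both figures.

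**The case against.** The strongest reply is that the objective is descriptive. The primary quantity is the prevalence of multimorbidity with 95% confidence intervals. Crude prevalence by group is the actual burden, age structure included, and the Lay Summary names planning and distribution of resources as a use. The template exempts purely descriptive studies from a confounding plan. This stands: crude prevalence should remain, and the fault arises only when the contrasts are read as effects or predictors.

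A second reply is that "We will adjust for confounding using multivariable regressions with random-effects models" covers all six Aim 1 characteristics and is not restricted to any aim. This also stands. A reader might infer that adjustment has been ruled out for Aim 1, but the text does not say so. What is missing is the link to a model.

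A third reply is that the choice of model or standard population can be left to a statistical analysis plan. That is fair for such details. It does not cover the comparison method, because the protocol has already chosen one.

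Finally, the illustration rests on assumed inputs. It has a 21-point gap in the share aged 18-44 and implies about 26% prevalence overall rather than 23.2%. It shows what can happen and is not a forecast.

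**Conclusion.** The point holds as an improvement that costs almost nothing. The Aim 1 comparisons, and the Aim 2 comparison of pairs by covariate, are specified without adjustment, and the promised age-adjusted regression is attached to no model with multimorbidity as outcome. Because the protocol elsewhere speaks of predictors and impact, the contrasts by ethnicity, deprivation, smoking and region are open to distortion by age in either direction. Under the assumptions shown, age mix alone gives gaps of 1.3 to 15.2 points, with 27.0% against 18.1% (odds ratio 0.60) as the worked case.

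Two stronger conclusions are tempting but unsupported. A reader might infer that the crude differences will mainly reflect age structure. The documents contain neither age-specific prevalences nor age mixes by group, so that share is unknown. A reader might also infer that tests on some 405,000 patients are uninformative. They add little to estimates with intervals, but the 0.26-point threshold applies to two equal halves, smaller groups are less sensitive, and the protocol already commits to confidence intervals for prevalence. The sample size and the overall prevalence estimate are unaffected.

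**What to change.** Keep crude prevalence with 95% confidence intervals, by group, as the description of burden. Add to Aim 1 one or both of the following:

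- Age- and sex-standardised prevalence by ethnicity, IMD decile, smoking status and region.
- A logistic model for two or more morbidities, and a count model for the number of morbidities, adjusted for at least age and sex with a practice random effect.

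Report differences or odds ratios with 95% confidence intervals alongside any p-values. Apply the same adjustment to the Aim 2 comparison of disease pairs by covariate. In the Plan for addressing confounding, name the aims and outcomes that it covers. If the authors prefer to stay with crude comparisons, the wording on predictors and impact should be limited to crude description.

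The cost is a small amount of extra analysis. All the variables are already in the planned dataset, and the protocol restricts the sample to patients with complete age, gender and IMD. No new data, linkage or patients are needed.

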In addition to the demands that multimorbidity places on GPs, multimorbidity is also a serious concern at both the patient and healthcare system level. In individuals, multimorbidity has been associated with higher incidence of acute diseases^7^, increased rates of disability^8^, increased mortality^1^, and decreased quality of life^8^. At the healthcare delivery level, multimorbidity has been associated with greater outpatient and inpatient health service utilization^4,9^, as well as with significantly increased healthcare expenditure on multimorbid patients compared to those with zero or one morbidity^10,11^.

Research on the epidemiology of multimorbidity and its relationship to health service utilisation plays an important role in informing the planning, organization, and delivery of health services to patients with multimorbidity^6^. Salisbury, *et al.*  used GPRD data to conduct research on multimorbidity and health service utilization, and found that people with multimorbidity had higher rates of GP consultations and less continuity of care^6^. Another metric that has been used to assess health service utilisation using CPRD/GPRD data is the number of prescribed drugs^12^. In their 2013 study, Brilleman *et al.* reported that the number of prescribed drugs is the most powerful predictor of future consultations and health service utilisation^12^.

While limited in number, there have been a few studies, in addition to the aforementioned Salisbury *et al.* and Brilleman *et al.* studies, investigating multimorbidity using CPRD/GPRD data^13,14^. One study by Booth *et al.* found a strong association between obesity and multimorbidity^13^. However, they only used 11 chronic conditions in their definition of multimorbidity, which excluded a number of conditions that would reasonably constitute morbidities^13^. Another study by Brilleman *et al.* compared the ability of different measures of multimorbidity to predict future healthcare costs^14^. The results suggested that there can be large differences in the prevalence of multimorbidity, depending on which multimorbidity measure is used^14^. They also found that “the best performing multimorbidity measures were simple counts of the number of chronic conditions patients suffered from”^14^. We will use this “simple count” approach to define the number of comorbidities each patient has.

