The outcome of our descriptive analysis is the prevalence of multimorbidity, and we will define multimorbidity using a list of 36 comorbidities (Appendix 1). See Section D for the rationale for choosing these specific morbidities.

In addition to describing the prevalence of multimorbidity, as part of our descriptive analysis we are interested in the pairing and clustering of different comorbidities. To assess the frequency of the most commonly paired comorbidities, our outcome will be pairs of any two separate morbidities from the code list of 36 comorbidities. Additionally, to evaluate our final descriptive outcome relating to the prevalence of physical-mental health comorbidities, mental health comorbidities will be defined as Depression and Anxiety, Alcohol Problems, Dementia, Learning Disability, and Schizophrenia or Bipolar Disorder. All other morbidities will be defined as physical (See Appendix 1).

*Exposures and Outcomes for Secondary Research Objective:*

Our secondary research objective is to investigate the association between multimorbidity and health service utilisation. The exposure for this four-year retrospective cohort study is multimorbidity, which has been defined above.

We will consider three patient-level health service utilisation outcomes:

- the number of GP practice consultations (in-person or by phone)
- the number of prescriptions a patient has been issued
- the number of hospital admissions.

We will consider mortality as a secondary outcome of the retrospective cohort component of our study.

1. **Data/ Statistical Analysis**

*This section should cover both the analytic methods and also the analyses which are to be performed to meet all the specific aims listed earlier. It is important to ensure that this section is clear and specific about any comparisons which will be made*

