**Appendix 1: List of the 36 disease conditions to be included in multimorbidity count**

| Code | Condition | *Criteria* |
| --- | --- | --- |
|  |  |  |
| HYP | Hypertension | *Read Code ever recorded* |
| DEP | Depression and Anxiety | *Read code recorded in last 12 months OR >=4 anti-depressant prescriptions (excluding low dose tricyclics) in last 12 months OR >=4 anxiolytic/hypnotic prescriptions in the last 12 months* |
| PNC | Painful condition | *>=4 POM analgesics in last 12 months OR >= 4 specified anti-epileptics in the absence of an epilepsy Read code in last 12 months* |
| AST | Asthma (currently treated) | *Read code ever recorded AND any asthma prescription in the last 12 months.* |
| CHD | Coronary heart disease | *Read Code ever recorded* |
| DIB | Diabetes | *Read Code ever recorded* |
| THY | Thyroid disorders | *Read Code ever recorded* |
| RHE | Rheumatoid arthritis, other inflammatory polyarthropathies & systematic connective tissue disorders | *Read Code ever recorded* |
| HEL | Hearing loss | *Read Code ever recorded* |
| COP | COPD | *Read Code ever recorded* |
| IBS | Irritable bowel syndrome | *Read code ever recorded OR ≥ 4 prescription only medicine antispasmodic prescription* |
| CAN | New diagnosis of cancer in last five years | *Read code first recorded in last 5 years* |
| ALC | Alcohol problems | *Read Code ever recorded* |
| OPS | Other psychoactive substance misuse | *Read Code ever recorded* |
| CON | Constipation (Treated) | *≥4 laxative prescriptions in last year* |
| STR | Stroke & transient ischaemic attack | *Read Code ever recorded* |
| CKD | Chronic kidney disease | *Best of the last 2 GFR readings <60* |
| DIV | Diverticular disease of intestine | *Read code ever recorded* |
| ATR | Atrial fibrillation | *Read code ever recorded* |
| PVD | Peripheral vascular disease | *Read code ever recorded* |
| HEF | Heart failure | *Read code ever recorded* |
| PRO | Prostate disorders | *Read code ever recorded* |
| EPI | Epilepsy (currently treated) | *Read code ever recorded AND antiepileptic prescription in last 12 months* |
| DEM | Dementia | *Read code ever recorded* |
| SCZ | Schizophrenia (and related non-organic psychosis) or bipolar disorder | *Read code ever recorded/recorded in last 12 months OR Lithium prescribed in last 168 days* |
| PSO | Psoriasis or eczema | *Read code ever recorded AND ≥ 4 related prescriptions in last 12 months (excluding simple emollients)* |

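### The morbidity count holds one male-only condition and no female-only one, so the planned comparisons by sex are not like-for-like and should also be shown on the 35 shared conditions

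*Protocol*

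**What the plan says.** The Exposures, Outcomes and Covariates section fixes the outcome: "we will define multimorbidity using a list of 36 comorbidities (Appendix 1"). The Background makes the score an unweighted sum: "We will use this “simple count” approach to define the number of comorbidities each patient has". One row of Appendix 1 is "Prostate disorders", met by a code at any time in the record.

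Sex is the first characteristic named in the first specific aim, which is to "describe the epidemiology of multimorbidity by sex, age, ethnicity, socioeconomic status, smoking status, and region". The Data/Statistical Analysis section sets three tests that bear on sex:

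- First aim, mean count: "We will use a t-test to assess differences in the mean number of morbidities by sex".
- First aim, 2+ status: a chi-square test to "examine differences in presence of multimorbidity (0-1 morbidities versus 2+ morbidities) in relation to sociodemographic characteristics".
- Third aim: a chi-square test of any multimorbidity and of physical-mental comorbidity across the same covariates. Prostate disorders count as physical, because every condition outside the named mental health group does.

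None of these tests is described as adjusted. The rationale for the list in the Background, the four numbered limitations and Appendix 2 do not mention that one item is open to men only. No count restricted to shared conditions is planned.

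**The concern.** A comparison of a count between two groups is easiest to read when both groups can score on the same items. Here they cannot. A man with hypertension and a prostate code meets the definition of multimorbidity. A woman with hypertension and a long-term gynaecological condition does not, because the list has no row for her second condition.

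Part of any reported sex difference will therefore reflect the make-up of the list. At this sample size a small component of that kind can be statistically significant, and readers are likely to take it as a difference in disease burden. The Lay Summary says that understanding sociodemographic effects may help to target interventions, so this result may be put to use.

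**Working it through.** **1. The list.** Appendix 1 has 36 rows with 36 distinct codes. This agrees with the stated 36 conditions, and 36 × 35 / 2 = 630 agrees with the stated number of pairs. One row (PRO) is male-only. None is female-only. Cancer is a single row, "New diagnosis of cancer in last five years", open to both sexes. Without PRO there are 35 conditions and 35 × 34 / 2 = 595 pairs, so 35 of the 630 pairs can occur only in men.

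**2. The sample.** The Sample Size section gives P = 23.2%, d = 0.13% and 95% confidence. Then n = 1.96² × 0.232 × 0.768 / 0.0013² ≈ 405,000, as stated. Dividing 405,000 by 0.952 gives 425,420, against the stated 425,400. Patients without deprivation data are dropped, so about 405,000 is the relevant n.

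**3. Mean count.** For an unweighted sum:

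male mean − female mean = (difference on the 35 shared conditions) + (prevalence of PRO in men)

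The second term is exact and cannot be negative. The protocol gives neither the prevalence of PRO nor the SD of the count. The following assumes SDs of 1, 1.5 and 2 and equal numbers of each sex, with SE = SD × √(4/405,000):

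| Assumed SD | SE of difference | 1.96 × SE | Power, PRO at 2% of men | Power, PRO at 5% of men |
|---|---|---|---|---|
| 1 | 0.0031 | 0.0062 | about 100% | about 100% |
| 1.5 | 0.0047 | 0.0092 | 99% | about 100% |
| 2 | 0.0063 | 0.0123 | 89% | about 100% |

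If the sexes were equal on the 35 shared conditions, a PRO prevalence of about 0.6% to 1.2% would bring the expected difference to the 5% threshold. At exactly that prevalence the test would reject about half the time; above it, power rises quickly.

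**4. 2+ status.** Only men with PRO and exactly one other listed condition are moved across the cut. Assume 23.2% in both sexes otherwise. The SE of the difference is √(0.232 × 0.768 × 4/405,000) = 0.00133, or 0.13 percentage points. If such men make up 0.25%, 0.5% or 1% of all men (assumed), the shift is 1.9, 3.8 or 7.5 SEs, and power is 47%, 96% or about 100%.

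**5. Physical-mental comorbidity.** The same mechanism applies to men with a mental health condition whose only physical condition is PRO. The protocol gives nothing from which to size this group.

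**6. Regressions.** The outcomes are presence of a mental health comorbidity, numbers of consultations, prescriptions and hospitalisations, and mortality. None is the morbidity count or 2+ status, and PRO is not in the mental health group.

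**The case against.** The strongest reply is that nothing is being mismeasured. The study is mainly descriptive, and its outcome is defined as a count on a stated list chosen for clinical relevance. A prostate disorder is morbidity that the man really has. For that estimand the tests are correct. The Background notes that the literature has not agreed on how to define multimorbidity, and the study aims to replicate and extend the Scottish work, which argues for keeping the full list. Removing the prostate item would equalise the maximum score but would not ensure equal coverage of each sex's disease burden. A result with and without one condition could also be placed in a statistical analysis plan, which is not available here.

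Most of this stands. It defeats any proposal to drop the item from the list or to make 35 conditions the main basis of the analysis. It does not answer the narrower point. The protocol itself fixes both the list and the tests by sex, and a reader of the results could not tell how much of the difference comes from the male-only item.

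The sizes are also open to challenge. They rest on assumed values, and statistical significance here mainly reflects n: a shift of 0.02 conditions is only 0.02/1.5 = 0.013 of an SD of 1.5. The planned precision of 0.13% is a half-width for overall prevalence and is no yardstick for a difference between the sexes.

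**Conclusion.** The point holds as a limit on comparability. The comparisons by sex in the first aim, and the similar chi-square test in the third, contain a component that only men can contribute and that nothing on the list offsets for women. For the mean count it equals the prevalence of prostate disorders in men. Its direction is certain. Its size cannot be fixed from the protocol and depends on the assumed prevalence, SD and sex split shown above.

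Three stronger readings are tempting but not supported:

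- A reader might infer that men will appear more morbid overall, or that a female excess at older ages would be hidden or reversed. The protocol states no female excess and plans no comparison of the sexes within age bands in this analysis, so reversal is not shown.
- A reader might infer that the sex coefficients in the regressions are distorted in the same way. The asymmetry lies in the count as an outcome, and no planned regression has the count or 2+ status as its outcome.
- A reader might infer that the t-test and chi-square are invalid. They estimate differences in the listed count correctly; the caution concerns what those differences mean.

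**What to change.** Keep the 36-condition list for the headline prevalence and the main analyses. In the Data/Statistical Analysis section, add that the comparisons by sex (the t-test and chi-square test of the first aim, and the chi-square test of the third) will also be reported on the 35 conditions open to both sexes, beside the 36-condition result. Add the asymmetry to the limitations. Leave the regressions as they are.

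The cost is one derived count from data already to be extracted and a few extra lines of output. The small downside is two sets of sex-specific figures, one of which does not match the headline definition and must be labelled clearly.
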